### Study variables

The main dependent variable will be the number of hospital falls. A hospital fall will be defined as “the consequence of a non-intentional and sudden movement towards the floor from a more elevated position” in hospital settings.

Other independent variables related with the patient who experiences a hospital fall include: (i) sociodemographic and economic data (age, gender, marital status and level of education); (ii) time (hour and minute, day and shift work) of fall; (iii) patient position (from the bed with or without bedrails, sitting, walking, and so on) and witness of the fall (roommate, family member, healthcare professional or no witness); (iv) use/no use of footwear and kind (open or closed); (v) cause of fall (instability (general instability and balance loss), dizziness (syncope, fainting and cardiovascular accident), drug adverse effects (diuretics, anti-hypertension and other drugs), accident (event with no identifiable cause), ambient-related (dropped objects, obstacles and wet floor), fragility (extreme fragility or weakness) or others); (vi) location of the fall (hospital room, bathroom, corridor, public area or others); (vii) fall-related injuries and severity (no wound/no consequences, minor wounds (grazes and minor contusions), afflicting wounds (contusions requiring stitches, fractures and skull trauma) or others (not afflicting wounds but still in need of minor medical intervention)); (viii) number and kind of coexisting clinical conditions; (ix) prescribed drugs and their time of administration; (x) chronotype measured by the Horne-Östberg Questionnaire (1976); (xi) quality of life in terms of body functionality, physical limitations, body pain, social role or function, mental health, emotional limitations, vitality, energy or fatigue and general perception about own health; and (xii) general health status in terms of somatic symptoms, anxiety, insomnia, social dysfunction and depressive symptoms.

In the case of healthcare professionals, independent variables will be: (i) sociodemographic and economic data (age, gender, marital status, level of education, work experience and time worked in the unit); (ii) kind of contract and work unit; (iii) sleep pattern (quality and quantity of hours); (iv) chronotype measured by the Horne-Östberg Questionnaire (1976); (v) quality of life in terms of body functionality, physical limitations, body pain, social role or function, mental health, emotional limitations, vitality, energy or fatigue and general perception about own health; (vi) general health status in terms of somatic symptoms, anxiety, insomnia, social dysfunction and depression; and (vii) fatigue/sleepiness, attention and cognitive functionality.

Pre- and post-intervention will be:

***Step 1.*** Before implementing preventive measures: development of audits and seminars in order to improve, secure and control the registration of falls in hospitals and related factors, as well as others study variables (quality of life, functional status, chronotype, fatigue/sleepiness, attention and cognitive functionality). These interventions will be carried out by research nurses who are working in hospitals.

***Step 2.*** Implementation of a preventive measures programme: adjusted to the identification of temporal patterns of falls and relative risk factors of falls. As measures will be agreed with the managers of hospital centres, the interventions will be reflected in the official document of general objectives of the hospitals. Official document to which the personnel involved in the intervention have access. Preventive measures will be focused on organizational, educational and behavioural elements related to older people and healthcare professionals:

Support and instruction to the patient in preventive health measures (wear suitable footwear and, when necessary, include orthoses; repeated reminders to patients of the need to notify the team for any situation (getting up/lying in bed, going to the bathroom/shower, walking in the hallways, …)).Take extreme measures to prevent falls by healthcare professionals at times related to meals and transfers.Placing a poster encouraging the need to review medication(s) at admission and periodically through patient monitoring.Patient risk management procedures, including post-fall monitoring, alternatives to restrictions and/or restrictive elements, increased number of nursing visits to the patient, promotion of safe mobility and bathing practices based on specific clinical guidelines (Register Nurses’ Association of Ontario, 2011) and use of proper closed footwear.Monitoring and improvement in the distribution of work shifts in healthcare professionals.

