## Background

The proportion of older people in the general population has increased during the last few years. Consequently, an important challenge of the public health system is to preserve the autonomy and independence of this group. One of the greatest causes of loss of autonomy and independence are accidental falls and related injuries. Epidemiology shows that accidental falls are not only a main and common problem among older people all around the world but also a big issue in terms of social and economic repercussions for the victims and their families. [1]

Hospital falls imply a greater challenge for healthcare organizations due to their effect on the patient’s quality of life (due partly to the loss of autonomy and independence). In addition, they increase morbidity and length of stay in hospitals, leading to an important rise of the sanitary outlay [2, 3].

Falls in older people are due to intrinsic and extrinsic factors [4]. Even though many studies have been conducted to identify the causality of falls, the time of falls is often not considered [5]. Evidence suggests temporal patterns in the occurrence of hospital falls [6]. Research in temporal patterns in the manifestation and intensity of symptoms and risk of life-threatening and life-ending events (chronopathology and chronorisk) is essential to develop longitudinal (chrono)preventive and (chrono)therapeutic interventions and strategies that take into account the aforementioned patterns [7, 8]. Therefore, this study aims to implement longitudinal preventive counter-measures based on temporal patterns of incident events and relative risk factors for falls and related injuries (*chronoprevention*).

The risk of fall is directly correlated to ageing, so the number of accidental falls will proportionally grow with the ageing of general population [4, 9]. Recent studies show that 30 % of people living among their communities suffer one fall per year [10], rising to 40 % among hospitalized people [11]. Regarding hospitalized people, fall rates show a great variability, between 2 and 17 falls per 1,000 occupied beds [12, 13].

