## Methods/design

### Aims

The main aim of this study will measure the effect of the implementation of a falls prevention programme based on temporal patterns and relative risks factors.

Secondary aims will be: (i) to identify temporal patterns in the incidence of hospital falls and intrinsic and external risks factors, pre- and post-intervention; (ii) to establish differences in temporal patterns according to the hospital setting (teaching or non-teaching) and the different types of wards (medical, surgical or mixed), pre- and post-intervention; (iii) to study the role of circadian time in drug administration for older people suffering from hospital falls, pre- and post-intervention; (iv) to identify the level of fatigue/sleepiness, attention and cognitive functionality of healthcare professionals intervening during hospital falls, pre- and post-intervention; and (v) to develop a uniform, simple and intuitive method to record hospital falls in order to improve the effectiveness of the registration of falls and to assess the implementation pre- and post-intervention.

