### Design

A mixed-method research design will be carried out. Three different study designs will be used:

***Phase 1.*** Prospective longitudinal study in two steps:

A first step of 18 months, in which a first intervention of audits and seminars in healthcare professionals will be carried out, focused on an effective and efficient registry of hospital falls in older people. This first phase is crucial to identify temporal patterns of falls in relation to specific intrinsic and extrinsic risk factors among hospitalized older people, as well as the levels of fatigue/sleepiness, attention and cognitive functionality of the healthcare professionals who attend to an in-hospital fall.A second step of application of a multidimensional prevention programme for 15 months focused on organizational, educational and behavioural elements applied to admitted older people and healthcare professionals.

***Phase 2.*** Retrospective study of the fall records found in the institutional databases of the study centres in the period between January 2018 and September 2020. This period covers the first (January 2018–May 2019) and second phases (June 2019–September 2020) of the project, as previously indicated.

***Phase 3.*** Descriptive exploratory study with a qualitative approach, focus groups made up of healthcare professionals: doctors, nurses and nursing assistants who provide and have provided their professional services in the field of study, in the periods in which the longitudinal and retrospective studies have been carried out.

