After obtaining and analysing the falls that occurred during the first 18 months of the study, time-adjusted preventive measures will be carried out. These measures will be focused on organizational, educational and behavioural elements (previously mentioned).

The establishment of the programme of time-adjusted prevention measures will be carried out in May 2019 in the four centres. The post-intervention data collection will cover July 2019 to September 2020. The managers responsible for each centre, together with the research team, will implement the measures, and, as in the first phase, seminars will be held with healthcare professionals to focus on the recording of falls and their circumstances, as well as the variables included in the prevention programme.

During the post-intervention phase, the individual monthly audits will continue to be carried out with each Clinical Management Unit. This follow-up will make it possible to discern the effectiveness of the preventive measures.

***Phase 2***: For the retrospective study, the data will be delivered by the centres participating in the project to the Principal Investigator anonymized.

***Phase 3***: The development of the focus groups will be carried out in the facilities of the participating hospitals, ensuring the confidentiality of the participants. Four focus groups will be held at the Reina Sofia University Hospital in Córdoba and one in each of the three regional centres.

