### Data analysis

***Phases 1 and 2.*** For the analysis of quantitative data, descriptive statistics will be used, including measures of frequency, central tendency and dispersion according to the type of variable (quantitative or qualitative). Normality will be calculated with Shapiro-Wilk’s test and homogeneity with Levene’s test. To compare proportions of categorical variables, the chi-square test for contingency tables will be used. In the case of 2 × 2 tables, such tests with Yates correction will be used, and if the expected frequency is ≤ 5, Fisher’s exact test will be used. To compare mean values between the quantitative variables of two groups, Student’s t test for independent samples will be used. For the comparison of the mean values between quantitative variables and hospitals, the one-factor ANOVA test and ad-hoc tests with correction by GT2 Hochberg (if variance is homogeneous) or Games Howell (if variance is unequal) will be used. For the correlation between the quantitative variables, Pearson’s correlation coefficient will be used. For the logistic regression, multivariate analysis will be used.

All hypothesis tests will be bilateral. All tests with a confidence level of 95 % (p < 0.05) will be considered statistically significant.

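### The main outcome is a raw number of falls with no exposure denominator, although the before and after periods differ in length

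*Protocol article*

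**What the plan says.** The Aims section sets the question: "The main aim of this study will measure the effect of the implementation of a falls prevention programme". The Study variables section sets the outcome: "The main dependent variable will be the number of hospital falls". The Abstract and the Discussion both express the hoped-for result as a lower number of falls.

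The Design section gives the periods as "A first step of 18 months, in which a first intervention of audits and seminars in healthcare professionals will be carried out" and "A second step of application of a multidimensional prevention programme for 15 months". The Procedure section repeats the first length ("After obtaining and analysing the falls that occurred during the first 18 months of the study") and dates collection after the programme from July 2019 to September 2020, which is 15 months. The Phase 2 paragraph of the Design section divides the same 33 months differently, at the end of May 2019, which makes 17 and 16 months.

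Phase 1 enrols older inpatients who fall and who sign consent. Phase 2 takes institutional records of falls. The variables listed describe fallers and the nurses responsible for them; none is patient-days, admissions or occupied beds. The only denominator in the article is in the Background, for other studies: "between 2 and 17 falls per 1,000 occupied beds".

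The Data analysis section lists chi-square and Fisher tests, a "t test for independent samples will be used", one-way ANOVA, Pearson correlation, logistic regression and Cosinor fits. None is assigned to the main before-after question, and none is described as using exposure or period length.

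**The concern.** A number of falls depends on the fall rate, on how long one observes and on how many older patients are in bed. Only the first can reflect the programme. With the outcome fixed as a number, a drop may come from a shorter window or fewer bed-days. On either set of dates the second window is the shorter, so the length effect favours the programme.

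The listed tests do not repair this. Every enrolled patient and every collected record is a fall, so a chi-square test or logistic model on those data cannot estimate the risk of falling. The design has no concurrent control, so the conclusion on the main aim rests on this one comparison.

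**Working it through.** The article states no expected count, effect size or power, so there is no figure to reproduce. The check asks what a raw number shows when the fall rate has not changed.

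**Inputs from the article.** Periods of 18 and 15 months (Design, Procedure) or 17 and 16 months (Phase 2 dates in Design); two-sided tests at 5% (Data analysis).

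**Assumptions.** The post/pre ratio of monthly patient-days, *v*, and the total number of falls, *N*. The documents give neither.

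**1. Totals, constant volume (*v* = 1).** Apparent reduction = 1 − T_post/T_pre.
- 18 against 15 months: 1 − 15/18 = 16.7%. In calendar days, 1 − 458/546 = 16.1%.
- 17 against 16 months: 1 − 16/17 = 5.9%. In calendar days, 1 − 488/516 = 5.4%.

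**2. Totals, changing volume (18/15 split).** Apparent reduction = 1 − *v* × 15/18.

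| *v* (assumed) | 0.8 | 0.9 | 1.0 | 1.1 | 1.2 |
|---|---|---|---|---|---|
| Apparent reduction | 33.3% | 25.0% | 16.7% | 8.3% | 0.0% |

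**3. Monthly counts.** Period length cancels and the apparent change is 1 − *v*. At *v* = 0.9 an unchanged rate gives 10% fewer falls per month; at *v* = 1.1 it gives 10% more.

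**4. False-positive risk if two totals are compared as though exposure were equal.** Take Poisson counts, an unchanged rate and *v* = 1. Given a total of *N* falls, the second-period count is binomial with probability 15/33 = 0.4545 (or 16/33 = 0.4848). It is tested exactly against 0.5, two-sided at 5%. The chance of declaring a reduction, nominally at most 2.5%, is:

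| *N* (assumed) | 18/15 split | 17/16 split |
|---|---|---|
| 200 | 22% | 5% |
| 500 | 51% | 9% |
| 1,000 | 81% | 15% |

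This test illustrates the size of the problem; the article does not name it.

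**5. With a denominator.** Dividing falls by exposure gives a rate ratio of 1.00 at an unchanged rate, whatever the split and whatever *v*.

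**6. Calendar mix.** January 2018 to June 2019 contains January to June twice and July to December once. July 2019 to September 2020 contains July to September twice and every other month once. The Background reports that month of the year affects falls, so even a rate needs adjustment for month or season.

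**The case against.** A reader might infer that the study will report a spurious 17% reduction. The article does not support that. It nowhere says that two period totals will be compared, and two single totals could not enter the t test it lists, which needs replicate units. Audits take place monthly in each clinical unit, so monthly counts are a plausible unit, and they would remove the length artefact. The 17% also uses only one of two conflicting splits. Both objections stand, so the figures are conditional.

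A reader might also infer that no exposure data will be collected. The article supports only the statement that none is listed. Patient-days are routine administrative data, and the article speaks of incidence in a secondary aim and in the Discussion, which suggests that the authors think in rates. Nor do the documents show that bed-days fell: volume could have risen, and with a 20% rise the artefact in the totals disappears under the 18/15 split.

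Finally, a condensed article may leave the choice of count model to a fuller document. That is fair for the model. It does not cover the outcome, which the article states and states as a number. The word incidence is never given a denominator for this study, and a rate cannot be formed from the variables listed.

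**Conclusion.** The point stands in conditional form. The main outcome is fixed as a number of falls without exposure, across periods that are unequal on either reading of the dates. As worded, it cannot separate a programme effect from shorter observation or a change in the number of older inpatients.

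If totals are compared, at constant volume, the length artefact is about 17% (18/15) or 6% (17/16), in the programme's favour. If monthly counts are compared, the length artefact goes but any change in bed-days remains, with direction and size unknown. The 33% to 0% range rests on assumed volume ratios, and the false-positive rates rest on assumed totals and on a test the article does not name. The need for a denominator depends on none of these assumptions.

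**What to change.** - **Outcome.** Define it as falls per 1,000 patient-days in patients over 65. The numerator should be all recorded falls in that age group, not only those of patients who consent: consented fallers over everyone's patient-days is not a fall rate.
- **Denominator.** Obtain monthly patient-days for that age group from each hospital: 4 hospitals × 33 months = 132 hospital-months.
- **Analysis.** Estimate the post/pre rate ratio with a 95% CI by negative binomial or overdispersed Poisson regression of monthly falls, with log(patient-days) as offset, hospital as a factor and a term for calendar month or season.
- **Dates.** Reconcile the 18/15-month statements with the 17/16-month Phase 2 dates, and state which months belong to each period.

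The cost is one routine administrative data request per hospital, which can be made retrospectively, and a change to the outcome and analysis wording. No new patients are needed. A rate ratio corrects for exposure; it does not turn an uncontrolled before-after comparison into a controlled one.

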### Participants and setting

***Phase 1.*** The study subjects will be all those patients over 65 years of age who suffer one/several fall(s) during their admission to the Reina Sofia University Hospital in Córdoba and in the three regional hospitals of the Province of Córdoba (Cabra, Montilla and Pozoblanco) from January 2018 to September 2020.

Specifically, for the study of the levels of fatigue/sleepiness, attention and cognitive functionality of the healthcare professionals, the reference nurses of the older person who has an in-hospital fall during the study period will also be included.

***Phase 2.*** Institutional records of falls occurring in patients over 65 years old. In order to contrast with the prospective design, the institutional records of the four hospitals will be collected during the same period (January 2018 to September 2020).

***Phase 3.*** Healthcare professionals (doctors, nurses and nursing assistants) will be interviewed.

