### Data collection: Instruments

***Phases 1 and 2***: Several instruments will be used for data collection. The variables related to the fall and older person will be collected through the fulfilment of a specific record sheet for falls. This record sheet will have to be completed by the patient’s referring nurse (professional who generally records the fall, a fact documented in previous investigations [6]. The registration sheet will be the one attached at the end of this report, similar to that used in a previous project of the research group [20] (ANNEX I). To facilitate this process, an electronic data collection notebook will be hosted on the website of the study hospitals.

On the other hand, the sleep pattern will be measured by means of the Pittsburgh Sleep Quality Index (Spanish version) [29]. The chronotype of each person will be determined using the Horne-Östberg Morningness-Eveningness Questionnaire (Spanish version) [30]. For the quality of life related to health, the 36-Item Short Form Health Survey, version 2 (SF-36v2) (Spanish version) will be used [31], while for the general health status, the 28-Item General Health Questionnaire (GHQ28) (Spanish version) will be used [32]. The variables somnolence, fatigue and speed of response to the event will be measured by means of the Epworth Sleepiness Scale (Spanish version) [33].

With the intention of managing the data appropriately, an electronic data collection notebook will be developed by the Bioinformatics Unit of the Maimonides Institute for Biomedical Research of Córdoba.

***Phase 3***: The focus groups will be constituted with healthcare professionals—doctors, nurses and nursing assistants who provide and have provided their professional services in the field of study in the period previously indicated.

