### Data collection: Procedure

***Phase 1***: The project will be explained to the institutional managers of the centres included in the study, who will appoint a coordinator to ensure proper development and will work in coordination with the research team. In these meetings, the process of recording falls will be disclosed, as well as the other variables.

Prior to data collection, meetings will be held with those responsible for the Clinical Management Units and special mention will be made of the areas that are expected to have a greater number of events (internal medicine, neurology, trauma, rehabilitation, …). Additionally, the dynamics of data collection will be explained.

On the other hand, being focused more on healthcare professionals (especially nurses) from the different study centres, several seminars will be held (first intervention), explaining how data collection should be done, as well as the definition of variables included in the record sheet. Such seminars will be proportional to the number of workers in the different centres included, being distributed over different days so that the number of workers receiving information is as large as possible. In addition, specific audits will also be carried out in each Clinical Management Unit.

During the first 18 months of study development, each time a fall occurs, in addition to recording the circumstances of the fall, it is necessary to obtain the informed consent of the patient to know their quality of life, general functional status, sleep pattern and chronotype. In healthcare professionals, informed consent must also be obtained to know the previous variables, as well as the values of fatigue/sleepiness, attention and cognitive functionality. In this sense, as it has been commented on in the inclusion/exclusion criteria, these variables will only be known in the healthcare professionals responsible for the older person, who have visualized and/or attended the fall event, even though the fall may be the result of a collective lack of attention from all the staff and not from a single person.

Once the prospective data collection period has started (January 2018), monthly individualized audits will be carried out in the different Clinical Management Units, aimed at managing correct data collection. Furthermore, these audits will allow obtaining a perspective of the fall event in relation to the number and related circumstances.

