## Discussion

In a multi-causal adverse event such as a fall, a good initial evaluation of hospitalized elderly people and their registration is necessary. The results of the study, in addition to stimulating the epidemiological investigation of falls, are intended to prevent falls in the hospital setting. Obtaining temporal patterns in hospital falls allows establishing high-risk periods during the day. This fact may correspond to certain activities predictable in time. In this sense, previous studies applied in Italian hospitals have shown that the establishment of time-adjusted preventive measures has led to a decrease in the number of falls [20, 21]. All this will contribute to improvement in the safety of the individual, and as consequence of their health, environment (family environment) and social level (due to the decrease in costs that a decrease in dependency implies) [20].

Furthermore, the study interventions emphasize the importance of recording in-hospital falls and their circumstances, especially time. Therefore, it represents a change in health policy. In previous studies [6], a low incidence of falls has been detected in the hospitals of Andalusia, being less than 1 %, although 65 year olds are the population that suffers the most from these types of events, which is contradictory. Contradiction contrasted with other studies [24], where healthcare professionals showed that there is an underestimation of hospital falls. On the other hand, the previous studies that support the present project [20] found high incidences as a result of an appropriate registry of these events.

Nurses routinely need 24 h per day to care for patients, in many different settings and environments. The impact on physical and psychological well-being of shift work management and lengths of shifts have been largely studied [36, 37]. The findings emerging from these investigations are that anomalies of the circadian rhythm summed with the characteristics of shift workers may have a direct influence on the health of nurses [38]. The outcome to be analysed in the proposed study relate chronotype, sleep quality and health status of the nurse with the quality of clinical practice and ultimately patient safety.

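### The study works on how completely falls are recorded while counting recorded falls as its main outcome, and plans no check that recording stayed stable between the two periods

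*Protocol article*

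**What the plan says.** All references are to the protocol article.

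- **Outcome.** Under Study variables: "The main dependent variable will be the number of hospital falls". Under Data collection: Instruments: "This record sheet will have to be completed by the patient’s referring nurse". The outcome is therefore a count of falls that a nurse has recorded.
- **Intervention on recording.** Step 1, under Study variables, consists of "development of audits and seminars in order to improve, secure and control the registration of falls in hospitals and related factors". Data collection: Procedure calls this an intervention: "several seminars will be held (first intervention), explaining how data collection should be done". Design places these audits and seminars in the first step of 18 months.
- **Timing.** "Once the prospective data collection period has started (January 2018), monthly individualized audits will be carried out in the different Clinical Management Units". At the start of the programme, in May 2019 and in all four centres, "as in the first phase, seminars will be held with healthcare professionals to focus on the recording of falls and their circumstances". The same section says that the monthly audits go on after the programme has started.
- **Effect of registration on the count.** The Background describes under-registration of falls. The Discussion says that earlier work by the group "found high incidences as a result of an appropriate registry of these events".
- **Second source.** For Phase 2, Participants and setting states that "the institutional records of the four hospitals will be collected during the same period (January 2018 to September 2020", as a contrast to the prospective data. Data collection: Procedure says that these records are delivered anonymised.
- **Limitations.** This section says that the records depend on the staff, in the retrospective phase too. It does not mention that registration may change over time.

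**The concern.** A before-after comparison of recorded falls estimates a programme effect only if the share of true falls that gets recorded (the capture) is the same before and after. Here the study sets out to change that share, and the people who record are among the staff whom the seminars and the programme address. There are at least three routes to unequal capture:

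- a gradual rise during the baseline as training takes hold;
- a fresh lift from the seminars repeated with the programme;
- fatigue later on.

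The recording burden may also differ. Data collection: Procedure ties the consent and questionnaires after each fall to the first 18 months, and the Background names workload as a reason for poor recording.

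All four centres start the programme in the same month, so no concurrent group would show a drift in capture. The main conclusion is at stake: rising capture masks a benefit, and waning capture imitates one.

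**Working it through.** **Inputs from the article.** The steps last 18 and 15 months (Design). Tests are two-sided at 5% (Data analysis). The article gives no capture rate, expected number of falls or effect size, so there is no stated figure to reproduce. Every capture rate and fall count below is an assumption.

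**Identity.** Observed rate ratio = true rate ratio × (capture post / capture pre).

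**Hiding a real effect.** The observed ratio is 1.00 when capture post / capture pre = 1 / true ratio.
- True ratio 0.80: 1/0.80 = 1.25, so a relative rise of 25% in capture hides a 20% reduction.
- True ratio 0.70: 1/0.70 = 1.43, so a relative rise of 43% hides a 30% reduction.

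**No true effect, capture drifting.** Three assumed baselines:
- flat at 80%: mean 0.80;
- rising from 50% to 80% in 6 months, then flat: (6 × 0.65 + 12 × 0.80)/18 = 0.75;
- rising from 50% to 80% over all 18 months: mean 0.65.

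Two assumed post-periods: flat at 80% (mean 0.80), or sliding from 80% to 60% (mean 0.70).

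| Baseline | Post flat at 80% | Post sliding to 60% |
|---|---|---|
| Flat 80% | 0.80/0.80 = 1.00 | 0.70/0.80 = 0.875 |
| 6-month rise | 0.80/0.75 = 1.07 | 0.70/0.75 = 0.93 |
| 18-month rise | 0.80/0.65 = 1.23 | 0.70/0.65 = 1.08 |

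The false reduction of 12.5% needs a flat baseline followed by a slide. A rise in the baseline shrinks it to about 7% or turns it into an apparent increase.

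**Leaving out the first 6 baseline months.** With the 6-month rise and a flat post-period the ratio becomes 0.80/0.80 = 1.00. With the 18-month rise, capture runs from 60% to 80% over the remaining 12 months (mean 0.70), which gives 0.80/0.70 = 1.14. With a flat baseline and a slide it stays at 0.875. So this step removes an early rise, reduces a slow one, and does nothing about later decline.

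**Chance of p < 0.05 with an inert programme.** Treat the two totals as Poisson counts and let r = capture post / capture pre. With N recorded falls in 18 months, the expected post count is N × (15/18) × r, and z = ln(r) / √(1/N + 1/post count). For N = 200:
- r = 1.0: 5%
- r = 1.1: 15%
- r = 1.2: the post count is 200, z = 0.182/0.100 = 1.82, chance 45%
- r = 0.8: the post count is 133, z = −0.223/0.112 = −2.00, chance 51%

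For N between 100 and 400, r = 1.2 gives 25% to 73%, and r = 0.8 gives 29% to 81%.

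**The case against.** The best defence is that registration support is deliberately balanced. Audits run monthly in both periods, and recording seminars are held at the start of each. The planned contrast is therefore registration support against registration support plus programme, not an unaudited period against an audited one. Research nurses carry out the Step 1 audits and seminars, so the recording nurses do not work unchecked. This stands, and it makes a large step in capture less likely. It does not show that capture stayed constant, and no measurement of it is described.

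A reader might go further in three ways that the article does not support.

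- *That reporting and programme effect can never be separated.* This is too strong. Phase 2 draws on adverse event reports and clinical records for the same months, and overlapping months are what a check of Phase 1 capture needs. Nothing says that the anonymised records lack ward, date or hour. What is missing is a plan to use them for this purpose.
- *That aim (v), on the recording method, has no baseline.* Study variables defines pre-intervention as Step 1 and post-intervention as Step 2, so the aim has the baseline that the article gives it. A comparison with usual registration before January 2018 would be a different aim.
- *That capture certainly rises during the baseline.* Data collection: Procedure can be read as placing training before January 2018, whereas Design puts the seminars inside the 18 months. The timing is ambiguous.

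A rise in baseline capture would work against the programme. That does not make the bias conservative overall, because later fatigue works the other way and the net direction is unknown. The Limitations section admits that records depend on staff and that a trial could be less biased, but dependence on staff is not the same as change over time.

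**Conclusion.** The point holds as a matter of unverified stability, not as a simple switch from poor to good recording. The main outcome depends on nurse recording, the study acts on that recording in the baseline and again at programme start, the article itself links registration to measured incidence, and neither a concurrent control nor a planned check of capture guards the comparison. Moderate drift is enough to matter: a 25% relative rise cancels a true 20% reduction, a 12.5% relative fall produces a false one of that size, and a 20% shift either way with an assumed 200 baseline falls makes an inert programme significant about half the time (45% or 51%). The identity is exact. The sizes rest on assumed capture rates and counts, and the significance figures also on Poisson variation. The data can still be partly rescued, so this is something the sponsor should change rather than a fatal fault.

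**What to change.** 1. **Supporting outcome.** Add the rate of falls in the existing severity category for afflicting wounds (contusions that need stitches, fractures, skull trauma; item vii of the patient variables), analysed in the same way as all falls. If the estimate for these falls does not support a change seen in all falls, interpret that change with caution. A rule that asks only for the same direction would be weak, since an inert programme would often meet it by chance.
2. **Capture by period.** Have the planned Phase 2 records delivered with centre, ward, date and hour. Match them to Phase 1 without identity, and report by month or period the share of institutional falls that Phase 1 also recorded. Add a sensitivity analysis that leaves the first months of registration training out of the baseline.
3. **Limitation.** State under Limitations that registration may have changed over time and that the bias can go either way.

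**Cost.** A few more fields in an extraction already planned, a matching step and additional analyses. Serious-injury falls are fewer, so their interval will be wider. Staff record them too, so they are less sensitive to reporting but not immune. The two sources are not fully independent, so the matched share may overstate the level of capture; its change over time is more useful if that dependence is similar in both periods.

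Extending the extraction to before January 2018 is optional. It would describe what the registration drive did, but could not detect capture that declines after the programme starts.
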